Effects of efalizumab on psoriasis disease activity, infiltration of skin lesions by T-cells (and other leukocytes), and expression of inflammation-related genes was assessed in skin biopsies obtained from 13 patients in the MOA sub-study. Six of 13 patients were judged to have a good response to efalizumab based on decreased epidermal hyperplasia and elimination of keratin 16 immunostaining in week 8 biopsies. On average, T-cells were reduced about 50% in week 8 biopsies from skin lesions. Quantitative RT-PCR measures of disease-related or inflammation-related genes showed consistent reductions in K16, IL-12 p40, -interferon, STAT-1, IL-8, and iNOS in good responders (by the histologic definition of response). Quantitative suppression of inflammation-related genes correlated better with response status than quantitative reductions in T-cells within lesions. To the extent that the group of inflammation-related genes forms a functionally-linked pathway, all measures were grouped into a "pathway score" according to a multivariate statistical method developed by [name]. By the same techniques, a composite clinical response score was constructed using a combination of histologic response measures and K16 gene expression. Composite clinical responses were much more highly correlated with an inflammation pathway score compared to a T-cell infiltration score.

Our overall analysis of results obtained with peripheral blood T-cells and psoriatic skin lesions suggests that one of the most important mechanistic effects of efalizumab may be suppression of T-cell activation, leading to decreased production of -interferon and other inflammatory products regulated downstream by -interferon/STAT1. As this view would significantly alter the current hypothesis that efalizumab improves psoriasis mainly by reducing T-cell trafficking into inflammatory skin sites, our new hypothesis would be significantly strengthened through the study of additional patients. In addition, the study of new patients would provide the opportunity to explore the mechanism by which T-cell activation is broadly affected by relatively selective targeting of a single cell surface integrin.

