**B) Hypotheses:**

Psoriasis is mediated through a type-1 pathway that can be affected by blocking CD11a.

1. CD11a blockade correlates with suppression of Type 1 inflammatory gene products;
2. Functional blockade of T-cell activation will persist only while LFA-1 is blocked/ down-regulated by Efalizumab.
3. T-cell activation through TCR complex will be blocked by efalizumab
4. Efalizumab decreases VLA-4 expression and this will have the functional consequence of blocking cell adhesion to fibronectin (a VLA-4 ligand).
5. **Aim:**

Primary:

- To determine whether improvement of target plaque under therapy with Efalizumab is correlated with changes in expression of defined inflammatory genes in the target plaque, and to characterize the contribution of defined inflammatory genes to the overall psoriatic inflammation process at different time points.

Secondary:

- To assess the correlation between functional CD11a blockade and response to treatment.
- To determine the mechanism of action of efalizumab in psoriasis focusing on blockade of important surface proteins during immune synapse formation (including TCR, LFA-1, VLA-4).
- To determine alterations of circulating leukocytes during and after efalizumab treatment.

1. **Primary outcomes:**
2. Clinical improvement of target lesions as measured by the **“Clinical Response Score”,** a single composite score based on quantitative measurement of epidermal acanthosis, qualitative expression of Keratin16 (histochemistry assessment) and quantitative measurement of K16 mRNA.
3. Measure genomic modulation by efalizumab real time RT-PCR for a set of pre-defined disease associated genes.
4. Characterization of inflammation through integration of quantitative expression of mRNAs encoding IL-12, gamma-interferon, STAT1, iNOS and IL-8 into the **“Type 1 pathway score”** (composite score derived by a novel multivariate analysis program).
5. Measure broad genomic modulation of psoriatic genes on the mRNA level using Affymetrix arrays in conjunction with cluster analysis programs at baseline and day 84 in circulating leukocytes and cells within psoriatic skin lesions.
6. **Secondary outcomes:**

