This is an open-label study to investigate the mechanism of action of efalizumab (anti-CD11a). After a wash-out period from standard therapies, patients with moderate to severe psoriasis will be treated with subcutaneous injection of 1.0 mg/kg/week efalizumab for 24 weeks.

- Patients will be assessed by the PASI score and a modified, “linear PASI score”. Patients will also be categorized as “*responders*” and “*non-responders*” according to objective outcome criteria (**Clinical Response Score** and **Type-1 Pathway Score**). The primary goal is to study the cellular and genomic basis for therapeutic improvement or resistance to CD11a blockade.

At baseline, an index plaque will be selected for serial biopsy analysis. This plaque is located on the trunk, buttocks, or thigh (sensitive areas such as the face will not be biopsied). Punch biopsies will be performed from the index plaque at baseline (before treatment) and after 2, 6 and 12 weeks of treatment with efalizumab. The response to treatment at 12 weeks will be graded. Complete responders according to the **Clinical Response Score** will be defined as patients that reverse keratin 16 expression in conjunction with reversed acanthosis and normalized differentiation. The clinical responses will be graded from best to worst using a multivariate analysis technique that creates the “**Clinical Response Score**” based on a combination of epidermal thickness, the qualitative pattern of keratin 16 expression, and quantitative expression of keratin 16 mRNA. The stratification of clinical responses by this technique provides a measure of disease improvement that can be subsequently related to quantitative alterations in expression of other disease-related and inflammation-related genes.

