The impact of CD11a blockade on a functionally linked pathway of inflammatory genes will be measured by the **Type-1 Pathway Score**. The genes included in this pathway are central to the activation of type 1 T-cells (IL-12, -IFN) and to genes regulating downstream inflammation (STAT1, IL-8, iNOS, MIG, etc). Because multiple genes are multiple independent variables, the **Type-1 Pathway Score** will serve as a novel multivariate analysis scoring tool. This allows us to compare “clinical” response outcomes **(Clinical Response Scores**) to modulation of type 1 inflammation-related genes **(Type-1 Pathway Score**). We will study the extent to which a response outcome is related to the number of residual T-cells in treated lesions versus the quantitative levels of -IFN mRNA (a direct measure of T-cell activation in plaques).

- Broad gene expression analysis in psoriatic skin lesions and blood at baseline, at the primary study endpoint (12 weeks of treatment) will be performed using a combination of gene arrays and real-time RT-PCR techniques.
- Cellular mechanisms associated with reductions in activation-controlling surface proteins on circulating and lesional T cells before and during efalizumab treatment will be studied. Previous work showed that T-cell activation is significantly impacted by efalizumab and several activation-controlling surface proteins are down-regulated during active treatment. Peripheral blood T-lymphocytes will be analysed at baseline, week 12 and in 2 week intervals after the last dose of efalizumab. This will include an analysis of dendritic cells in the peripheral circulation.
- Preliminary data demonstrated that VLA-4, an integrin unrelated to LFA-1, was down-regulated by efalizumab. Here, we will explore the functional consequences of VLA-4 modulation by efalizumab using functional binding assays with fibronectin as a ligand. We will determine whether this alteration is caused by reduced synthesis of VLA-4 or altered intracellular trafficking of integrin molecules. This will be in conjuction with [name] laboratory.
- Phenotype of cell suspensions of shave biopsies will be determined at baseline, week 2 and week 12, particularly to classify DC populations.

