The response score correlated well with histological findings. Patients judged independently as complete responders were assigned scores between 2.5 and 5.5, partial responders were assigned scores between –2.0 and 0.5; non-responders between –5.5 and –3.5. Epidermal CD3+ T-cells on day 56 had a week correlation of .52 with the response score, while dermal CD3+ T-cells were virtually uncorrelated (r=0.12). The T-cell pathway score for both types of CD3+ T-cells was 0.38.

The correlation of u scores for individual cytokines on day 56 with the response score ranged from 0.18 (-IFN) to 0.66 (IL-12). The inflammation pathway score based on the expression of all five cytokines was 0.80. The correlation was smaller for all subsets, indicating that all cytokines contribute, as one would expect from cytokines on a single pathway. Eliminating a single variable from the pathway score had the smaller effects on the correlation for IL12 (-0.01) and -IFN (-0.03) than for IL-8 (-0.07), STAT1 (-0.19), and iNOS (-0.21), consistent with the hypothesis that the latter cytokines are further “downstream”.

Among the 12 patients in this study, three patients were neither superior nor inferior to any other patient and, thus, could not be assigned an informative score. Comparing the remaining four patients with a positive response score to the five patients with a negative response score by the pathway score yielded test statistic of 6.102 (2, 1 d.f.). While this is nominally significant (p = 0.0135, exact), it cannot be excluded that results based on a study where the smaller group has only four patients are confounded.

Since this is a mechanism of action study, where the consequences of false negative results (not continuing research on an important mechanism of action) are at least as severe as the consequences of false positive results (doing more research on the current drug, even if the mechanism of action should turn out to be different). Therefore, level () and power (1-) need to be chosen so that  for. Thus, to achieve the conventional 5% level, a power of at least 95% would be required. Assuming t the within group variation and correlation of the data observed above is representative for data in the proposed study, the above test statistic of 6.102 can be interpreted as the non-centrality parameter of the chi-square distribution with 1 df.

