**APPENDIX F**

**Research Blood Tests**

1. **IMMUNOHISTOCHEMISTRY AND IMAGE ANALYSIS**

Tissue sections will be stained with haematoxylin and eosin (H&E) and with purified mouse anti-human monoclonal antibodies to K16, CD3, CD8 and CD103. Biotin-labeled horse anti-mouse antibody will be used for amplification, with avidin-biotin complex and developed with chromogen 3-amino-9-ethylcarbazole. Epidermal thickness measures will be computed using National Institute of Health software (NIH Image 6.1), and positive cells will be counted manually using computer-assisted image analysis. Conformational states of LFA-1 will be analyzed where there are suitable antibodies available for immunohistochemistry.

1. **RT-PCR ANALYSIS**

The PAXgene Blood RNA System is a commercially available integrated and standardized system for the collection and stabiization of whole blood specimens and isolation of cellular RNA. As an alternative, CPT tubes may also be used for this purpose. We will collect blood samples at time points indicated in Appendix I. Genes of interest include inflammatory genes and those responsible for the phenotype of psoriasis (-IFN, TNF-, STAT-1, iNOS, IL-8, MIG, IP-10, IL-19, IL-20, IL-23); those representative of T-cell activation (IFN-, IL-12, CD25); dendritic cell activation (CD80, IL-12); keratinocyte proliferation (Keratin 16); Type 1 or Type 2 T-cell immune deviation (-IFN , IL-4, IL-10, IL-11) and new genes discovered from gene chip data (ENRAGE, MMP). Other genes may be studied as they are discovered or their relevance is newly appreciated.

RNA will be extracted from tissues frozen in liquid nitrogen using the RNeasy Mini Kit. The primers and probes for the TaqMan RT-PCR assays for chosen genes have been generated using the Primer Express algorithm, version 1.0, using published genetic sequences (NCBI-PubMed) for each gene. The RT-PCR reaction will be performed using EZ PCR Core Reagents according to the manufacturer's directions. The samples will be amplified and quantified on an Applied Biosystems PRISM 7700 using the following thermal cycler conditions: 2 min @ 50C; 30 min @ 60 C; 5 min @ 95C; and 40 cycles of 15 sec @ 95C followed by 60 sec @ 60C. The human acidic ribosomal protein (hARP) gene, a housekeeping gene, will be used to normalize each sample and each gene. The data will be analyzed and samples quantitated by the software provided with the Applied Biosystems PRISM 7700 (Sequence Detection Systems, ver.1.7).

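### The K16 staining grade and the manual T-cell counts depend on the reader, and this open-label protocol does not mask that reader to visit, clinical response or gene results

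*Protocol*

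**What the plan says.** The Synopsis states: "This is an open-label study to investigate the mechanism of action of efalizumab (anti-CD11a"). Every patient receives efalizumab.

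The Clinical Response Score, under Primary outcomes, combines epidermal acanthosis with "qualitative expression of Keratin16 (histochemistry assessment) and quantitative measurement of K16 mRNA". The Synopsis defines complete responders as "patients that reverse keratin 16 expression in conjunction with reversed acanthosis and normalized differentiation", so a reading of K16 staining can decide whether a patient meets that definition.

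Appendix F (Immunohistochemistry and Image Analysis) gives the reading methods. For thickness: "Epidermal thickness measures will be computed using National Institute of Health software (NIH Image 6.1"). For stained cells, CD3 and CD8 among them: "positive cells will be counted manually using computer-assisted image analysis".

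The Synopsis also plans to study how far response is "related to the number of residual T-cells in treated lesions versus the quantitative levels of" interferon mRNA. This follows the earlier sub-study, where "Composite clinical responses were much more highly correlated with an inflammation pathway score compared to a T-cell infiltration score" (Preliminary Findings from Mechanistic Studies).

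Two places come near to a rule on readers. Appendix A asks that one evaluator do all PASI ratings for a subject, which is continuity rather than masking. The Statistical Model section says "Patients judged independently as complete responders were assigned scores between 2.5 and 5.5", but that describes the earlier sub-study and is not carried into this trial. Blinding is otherwise mentioned only for earlier efalizumab trials.

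**The concern.** Two of the trial's tissue readings rest on human judgement: a qualitative staining grade and a manual count. The results they will be set against come from RT-PCR. If the reader knows how a patient has done clinically, or has seen that patient's gene values, borderline K16 grades can drift toward what is expected. That creates agreement between the response score and the gene score that the tissue does not contain.

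The second issue is an asymmetry. The investigators want to test suppression of T-cell activation against the prevailing view that efalizumab reduces T-cell trafficking. Activation is represented by a machine-read mRNA level, and T-cell number by a manual count. Reader error or expectation therefore enters only one side of that comparison. The earlier sub-study reported 0.80 for the inflammation score and 0.38 for the T-cell score against response, and this trial revisits that contrast.

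This is not a matter to leave to an analysis plan. Appendix F fixes assay conduct down to the chromogen, software version and thermal-cycler settings, and a later analysis plan cannot mask slides that have already been read.

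**Working it through.** The plan gives no figure on this point, so the check has three steps: which readings depend on a person, how far a changed K16 grade moves the score, and how far drift could inflate the primary test.

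**1. Reader dependence of each measure**

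| Measure | Used in | How it is read |
| --- | --- | --- |
| Epidermal thickness | Clinical Response Score | Software (Appendix F) |
| K16 mRNA | Clinical Response Score | RT-PCR (Appendix F) |
| K16 staining | Clinical Response Score; complete-responder definition | Qualitative grade |
| T-cell number | Comparison with interferon mRNA | Manual count with image-analysis aid |
| Interferon mRNA and other pathway genes | Type-1 Pathway Score; same comparison | RT-PCR |

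One of the three response-score components depends on a reader. T-cell counts are not in that score.

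**2. Leverage of one K16 grade**

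Under the Statistical Model's rule, patient A gains a point over another patient only if A is higher on every variable, loses one if lower on every variable, and otherwise gets nothing. A changed K16 grade can therefore create or remove an ordering only where thickness and K16 mRNA already agree. It cannot by itself reverse one.

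The sample size used is the plan's own: 14.37 / 6.102 × 9 × 1.25 = 26.49, rounded up to 27. With 27 patients a score runs from −26 to +26. Using a two-level grade, assumed correlations of 0.3 to 0.8 among components, and ties allowed in the ordering:

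- Flipping one patient's grade moves that patient's score by about 5 to 6 points and changes its sign in about 8% to 16% of cases.
- Flipping five grades leaves a rank correlation of 0.96 to 0.97 with the unflipped scores.

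The grade influences the score but does not determine it.

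**3. Inflation of the primary test**

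The simulations use 27 patients, no true association between response and genes, and a three-level K16 grade. A stated share of grades is moved toward the gene result (one step in A). The table shows how often a nominal 5% test rejects.

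| Setting | None moved | 20% moved | 40% moved |
| --- | --- | --- | --- |
| A. Written rule, toward pathway score, 3,000 runs | 5.6% | 7.0% | 11.2% |
| B. Independent repeat of A, component correlation 0.6, 3,000 runs | 5.5% | 7.3% | 14.2% |
| C. Toward pathway score, component correlation 0.5, 2,000 runs | 5.3% | 7.5% | 14.4% |
| D. As C, toward a single gene | 5.3% | 5.7% | 9.6% |
| E. As B, ties allowed in the ordering | 4.7% | 5.1% | 6.5% |

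Simulation error in A: the 20% case exceeds its baseline by 7.0 − 5.6 = 1.4 points. The standard error of that difference is √(0.056 × 0.944 / 3,000 + 0.070 × 0.930 / 3,000) = 0.0063, or 0.63 points, so the excess is 1.4 / 0.63 = 2.2 standard errors. The 40% case is well outside simulation error.

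The shares, the component correlations and the form of the drift are assumptions; the protocol gives no basis for any of them. The simulations cover only the K16 route. No magnitude was derived for the T-cell counts.

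**The case against.** The strongest reply is that silence is not unmasked reading. Appendix F does not say who reads the slides, in what order or with what information, and a laboratory procedure that is not shown might cover it. That stands as a limit on wording: the protocol provides no masking, but it does not order unmasked reading.

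The K16 mechanism is also narrower than it first appears. The pathway score is relative, so it does not exist until the cohort's gene data are assembled, and the Data and Safety Monitoring Plan keeps data out of spreadsheets until final analysis. A reader is more likely to know the visible clinical response or single gene values, which is the weaker setting D. Knowing the visit adds little to the primary correlation, because all patients are compared at Day 84. These points stand and reduce the size. They are not masking.

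A reader might infer more than the documents support:

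- That both readings decide both analyses. K16 grading enters the response score and the counts enter the T-cell comparison. Neither enters both.
- That the laboratory reading the slides runs RT-PCR on the other half of the same biopsy. Appendix F assigns half a 6 mm biopsy to RNA for gene arrays. For RT-PCR it says only that RNA comes from frozen tissue, and it does not link the slide reader to the PCR results.
- That the T-cell comparison is biased toward the activation hypothesis. Unmasked counting could weaken or strengthen the T-cell correlation. Manual counting with image-analysis support is not a fault in itself.

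Finally, the person who codes slides should not read them, so two people are involved. That is a fair point about cost, but existing staff can do the coding and no additional reader is needed.

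**Conclusion.** The concern holds in a limited form. Two reader-dependent measurements feed, respectively, the primary response score and the T-cell number versus interferon mRNA comparison, and the protocol has no safeguard for either reading.

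For K16, the likely effect on the primary test is modest: about 7% rejection at a nominal 5% if one grade in five drifts, and about 11% to 14% if two in five do, under the written scoring rule with drift toward the pathway score. It is smaller if drift follows a single gene (5.7% and 9.6%) or if ties are allowed (5.1% and 6.5%). Material inflation therefore needs a large share of moved grades. For the T-cell counts, distortion is possible, but neither its size nor its direction can be established from the document.

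This is an inexpensive improvement in conduct that should be made. It does not show that the trial's result would be wrong.

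**What to change.** Add to Appendix F, under Immunohistochemistry and Image Analysis:

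- Existing staff other than the reader code the slides.
- Each patient's biopsies are read in random order, after that patient's Day 84 biopsy has been taken.
- The reader does not know visit, PASI or RT-PCR results.
- K16 grades and CD3 counts are locked before they are linked to the gene data.

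The cost is the coding work and a short delay before slides are read. No extra reader, biopsy or patient is needed, and treatment does not change.

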This study will be conducted according to the International Conference on Harmonization E6 Guideline for Good Clinical Practice (GCP) and any federal, national, and local requirements.

Subject Discontinuation

Subjects may withdraw or be withdrawn from the study, at any time. Every effort will be made to obtain information on subjects who discontinue from the study prematurely. The procedures and assessments to be performed at the end of treatment visit will be the same as those for the Day 84 visit.

Criteria for Discontinuation of Treatment

The criteria for discontinuation of treatment include the following:

- Pregnancy
- Administration of a live virus or bacteria vaccine
- Initiation of excluded systemic treatment for psoriasis
- Initiation of excluded immunosuppressive treatment for any indication
- Initiation of excluded experimental medication or other treatment
- Any medical condition (e.g., opportunistic infections, malignancies, immune complex disorders) that the investigator determines may jeopardize the subject’s safety if he or she continues in the study.

Study Discontinuation

Genentech has the right to terminate this study at any time. Reasons for terminating the study may include the following:

- The incidence or severity of adverse events in this or other studies indicates a potential health hazard to subjects.

1. **Statistical Model**

Preliminary data suggest that patients responding to efalizumab have lower expression levels of cytokines associated with activation of T-cells (IL-12, -IFN, IL-8, iNOS, and STAT1) than patients not responding. The response had been determined by the expression of K16 mRNA and epidermal thickness on day 56.

To correlate overall response with overall cytokine expression, response and cytokine expression were scored using a novel application of u-statistics to multivariate data. In short, the (response or cytokine expression) profile of each patient (A) is compared one-by-one with the profiles of all other patients (Xi). If patient A has a higher observation for each of the (response or cytokine expression) variables than patient Xi, the score of patient A is increased by one, if all Xi variables are lower, the score is decreased by one. If some variables have higher observations, while others have lower observations, the score of patient remains unchanged.

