1. **GENE EXPRESSION**

Gene chip studies will be performed as previously published by our group (Ostreicher et al, *The Pharacogenomics Journal,* 2001, 1, 272-287). Total RNA will be isolated from one half of a 6 mm full thickness skin biopsy using the Rneasy mini kit (Qiagen) and amplified using RiboAmp OATM RNA Amplification Kit (Arcturus). Labeled microarray targets will be prepared, and these will be hybridized to oligonucleotide arrays comprised of 12 000 known human genes (HuGeneU95 Av2, Affymetrix), for detection of fluorescence. Data analysis will be performed on raw fluorescent intensity values using GENECHIP 3.2 software (Affymetrix) or GeneTrafficTM.

1. **SATURATION ASSAY**

This competitive assay is performed by incubating PBMCs obtained during and after treatment with an anti-CD11a antibody (clone 25.3, Immunotech) which recognizes a different epitope than efalizumab. Stained cells will be analyzed by FACS to determine the percent binding with efalizumab.

1. **VLA-4 BINDING TO FIBRONECTIN AND ICAM-1**

Our laboratory will collaborate with [name] to confirm a previous finding in a small group of patients of decreased binding of T-cells to fibronectin, a VLA-4 ligand.

1. **T-CELL ACTIVATION ASSAYS**

T-cell activation will be assessed using a variety of techniques that are described below. We will need to work out methods so that down-regulation of surface receptors , e.g., LFA-1, TCR chains, and CD2, is maintained during an in vitro assay. Short-term activation-related assays (activation assessed within 4-6 hours) can probably be done on purified cell populations, but longer term assays will probably need to be done in whole blood preps or in purified cell populations to which autologous serum or efalizumab antibodies at an expected serum concentration is added. In turn, we need to establish a time-course for re-expression of various surface proteins after incubation in vitro with cells “washed” of exogenous or free efalizumab. Since we have not been able to reproduce receptor down-regulation by in vitro incubation of PBMC preps with exogenous efalizumab, we must work out re-expression kinetics and assay conditions on the first several patients that will be entered into this trial.

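### K16 mRNA in the Clinical Response Score and all five Type-1 Pathway Score genes are normalised to hARP, so hARP variation common to a biopsy can correlate the two scores; no RNA-free response analysis is planned beside them

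*Protocol*

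**What the plan says.** The primary aim, in the protocol section on hypotheses and aims, is "To determine whether improvement of target plaque under therapy with Efalizumab is correlated with changes in expression of defined inflammatory genes in the target plaque". The two scores that serve it are defined there under Primary outcomes:

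- The Clinical Response Score is "a single composite score based on quantitative measurement of epidermal acanthosis, qualitative expression of Keratin16 (histochemistry assessment) and quantitative measurement of K16 mRNA".
- The Type-1 Pathway Score is the "integration of quantitative expression of mRNAs encoding IL-12, gamma-interferon, STAT1, iNOS and IL-8 into the" composite.

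Appendix F, RT-PCR Analysis, sets the normalisation: "The human acidic ribosomal protein (hARP) gene, a housekeeping gene, will be used to normalize each sample and each gene". It names no second reference gene. Of the tissue source it says "RNA will be extracted from tissues frozen in liquid nitrogen using the RNeasy Mini Kit". It does not say whether one extract and one hARP reading serve all six genes. T-cells, epidermal thickness and K16 protein are measured on stained sections (Appendix F, first item).

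The Synopsis plans to compare the two scores. It also plans to ask whether response follows the number of residual T-cells or the level of gamma-interferon mRNA. The preliminary findings already report that "Composite clinical responses were much more highly correlated with an inflammation pathway score compared to a T-cell infiltration score".

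Scores are built by pairwise comparison of patients (Statistical Model), with the rule "If some variables have higher observations, while others have lower observations, the score of patient remains unchanged".

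**The concern.** When two quantities are divided by the same noisy third quantity, they correlate even if they are otherwise unrelated. If hARP in a biopsy reads low, K16 mRNA and all five inflammatory genes read high together; if it reads high, they all read low. That pushes the response score and the pathway score in the same direction, which is the direction of the primary hypothesis.

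T-cell counts have no hARP term. A comparison of gene measures with T-cell counts as correlates of response is therefore uneven. This comparison bears on the protocol's main scientific question: whether efalizumab acts mainly by suppressing T-cell activation or mainly by reducing trafficking into skin. The protocol describes no analysis that would show how much of an observed association depends on the shared normaliser.

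**Working it through.** **The plan's own figures.** The Statistical Model gives 14.37/6.102 × 9 × 1.25 = 26.49, hence 27; with 10% dropout, 27/0.9 = 30. Both reproduce. The pilot statistic 6.102 on 1 df gives p = 0.0135, as stated. I use n = 27 below. The protocol gives no figure for hARP error, so I show a range.

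**Pairwise effect.** On the log scale, write K16 mRNA as K − h and a pathway gene as G − h. K and G are independent with SD 1, and h is the common hARP error with SD r. The covariance is r² and each variance is 1 + r², so the induced correlation is r²/(1 + r²):

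- r = 0.25: 0.0625/1.0625 = 0.06
- r = 0.5: 0.25/1.25 = 0.20
- r = 0.75: 0.5625/1.5625 = 0.36
- r = 1: 1/2 = 0.50

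**Effect on the scores.** Two of the three response items carry no hARP, and discordant pairs do not count, so the effect is diluted. I simulated 27 patients with 3,000 replicates per r and no link between response and genes. Assumptions: within-block correlation 0.5, K16 staining at three levels with ties permitted, and the same log hARP error subtracted from K16 mRNA and all five genes. Two tests at a nominal two-sided 5% were applied: Spearman between the scores, and the pathway score compared between patients with positive and negative response scores, which is the pilot's comparison (Kruskal–Wallis). Repeat runs differ by about one percentage point.

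| r | Mean score correlation | Spearman rejects | Two-group test rejects | Spearman, K16 mRNA left out |
|---|---|---|---|---|
| 0.25 | 0.03 | 5% | 4% | 4–6% |
| 0.5 | 0.11 | 8% | 7% | 4–6% |
| 0.75 | 0.20 | 16% | 12% | 4–6% |
| 1 | 0.27 | 26% | 19% | 4–6% |

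**Sensitivity to assumptions.**

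- Within-block correlations from 0.7/0.5 to 0.3/0.1 (response block/gene block): a Pearson test rejects 6–12% at r = 0.5 and 28–37% at r = 1; the two-group test rejects 6–10% and 19–29%.
- Scoring rule read strictly, so that tied K16 staining makes a pair uninformative: the two-group test rejects about 6% at r = 0.5 and 8–9% at r = 1.
- Independent hARP readings for K16 and for the pathway genes: the induced correlation is about 0.

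**Contrast with T-cell counts.** I added a two-count T-cell score, also unrelated to response. The pathway score has the higher correlation with response in 55%, 65–67%, 75–76% and 84–85% of trials at r = 0.25, 0.5, 0.75 and 1. Without K16 mRNA in the response score the figure is about 50%, as it should be.

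**The case against.** - **A single hARP reading is not written.** This stands. Appendix F says that hARP normalises every sample and gene, not that one reading from one extract is reused. A reader might infer a single shared reading, but the text does not establish it. Separate readings would remove independent reading error. They would not remove real variation of hARP in the plaque, which stays common to genes measured in the same biopsy.
- **Normalisation removes shared error too.** This stands. Scarce RNA lowers targets and hARP together, and the ratio corrects for it. The simulation puts error in the divisor only, so r must be read as the hARP error left after that benefit. Dropping the normaliser is no remedy.
- **The pilot shows no strong artefact.** Gamma-interferon mRNA, which on the planned method carries the hARP term, correlated only 0.18 with response, against 0.52 for epidermal T-cells. This is fair but weak evidence: with 12 patients, the 95% interval for 0.18 runs from −0.44 to 0.68.
- **The pattern was also seen against histology.** The preliminary findings report that gene suppression tracked response status better than T-cell reductions did, with response judged from hyperplasia and K16 immunostaining. This stands: the activation hypothesis does not rest only on a score containing K16 mRNA.
- **A section-only response score has its own shared source.** It comes from stained sections, as the T-cell counts do. This stands and must be declared with the result.
- **The SAP may add sensitivity analyses.** Possible; it is not shown. The point here concerns the normaliser and the score composition, both of which the protocol fixes.

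**Conclusion.** The mechanism and its direction follow from what the protocol fixes: K16 mRNA in the response score, five mRNAs in the pathway score, and hARP for all of them. The size does not follow from the documents. Under the main assumptions there is no inflation at r of 0.25 or less. At r = 0.5 the rejection rate is about 7–8%, and at r = 1 about 19–26%, depending on the test. Tie handling and within-block correlation move these figures further, as shown.

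A reader might infer that the pilot correlation of 0.80 is a normaliser artefact. The documents do not support that. In a pilot-like setting (12 patients, two-item response), hARP error alone at r = 1 gives a mean correlation of 0.30–0.36 and reaches 0.80 in only about 1% of runs. A reader might also infer that K16 mRNA must leave the primary score. That is not shown either: r is unknown, and the 6.102 behind the sample size came from a response based on K16 mRNA and epidermal thickness, so replacing the score would detach the study from its sizing basis.

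Severity is moderate. No change in sample size follows.

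**What to change.** Keep the three-item Clinical Response Score as planned. Prespecify the following beside it:

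1. The same correlation with the Type-1 Pathway Score, using a response score from epidermal thickness and K16 immunostaining only.
2. The comparison of gene measures (pathway score and gamma-interferon mRNA) with T-cell counts on that RNA-free score.
3. A report of hARP variability across biopsies, with a statement of whether one hARP reading serves all genes of a sample.
4. A rule that gene expression is said to outperform T-cell counts only if this also holds on the RNA-free score.

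The cost is analysis wording; no new samples are needed. The two-item score separates patients less finely. It also shares its tissue-section source with the T-cell counts, and the report should say so.
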